| Study Method/ Design | This will be 2 parallel-group randomized controlled trial with 1:1 allocation ratio to usual care or intervention (PP).  The control group will be usual care in all participating departments/hospitals. The prone position will not be allowed during the day (allowed at night if it is the patient’s natural sleeping position).  The intervention group will undergo the following:   - Each day of hospitalization, at least 2 PP sessions during the day, with the objective to spend as much time as possible in PP if tolerated and a minimum of 2.5 hr cumulative time in PP during the day. - A session of PP as long as possible at night. Patients will be encouraged to sleep in PP as much as possible at night, knowing that monitoring the number of hours will not be feasible in COVID-19 medical wards in the current context.   Bedridden patients who are not able to self-position to the prone position or with minimal assistance of one person will not be included in the study.  Barriers will be positioned to avoid a potential fall out of bed.  The patient will be allowed to choose the best PP as long as the back of the thorax is not compressed by the bed. |
| Inclusion criteria | Patients > 18 and < 85 years old  Patients hospitalized with a laboratory-confirmed SARS-CoV-2 infection  Patients on oxygen therapy (nasal cannula, mask or high-flow nasal oxygen therapy)  Patients able to self-position to the prone position or with minimal assistance of one person  Signed the consent form  Patients hospitalized in a COVID-19 medical ward for < 72 hr |

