### Drawback of PP during spontaneous breathing

The mean duration on PP was 2 hr in spontaneously breathing patients in the study by Ding et al. (DING; Crit Care; 2020). For our study, to obtain an optimal benefit, we propose a minimum of two PP sessions during the day with a minimum cumulative time of 2.5 hr.

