## Research-Specific Procedures

### Prone position

1. Preparation

Check that all cables and lines (if present) are mobile enough to allow the patient to perform the self-prone position.

Explain the procedure to the patient:

- Perform a minimum of 2 prone position sessions during the daytime.
- With an objective of a cumulative time of at least 2.5 hr in the prone position during the daytime. The objective is to lie as much as possible in the prone position if it is possible.
- Patients will be able to move their head as they desire.
- The leg can be slightly bent to discharge the hip.
- Patients can change their bent leg as they wish while the spine remains free.
- The arms can be along the body or one arm can bent or both arms can be bent as in the picture below.

[figure not shown]
The position should be as comfortable as possible for the patient.

1. How to process the positioning

- Note the date and time of the beginning of the prone position in the notebook (by the patient or by a staff member).
- Ask the patient to lie on the stomach and place the barrier to prevent a potential fall out of bed.
- Make sure the patient is comfortable and explain that they can move themselves in the bed but the back should always be kept free to avoid compression of the lungs in the back region.
- Patients can turn slightly to a more comfortable position.
- The call bell is given to the patient so that they can call a staff member for assistance before each position change.
- Explain to the patient to not position themselves in the PP or supine position but use the call bell so that someone can help and set the barriers (the patient is informed that they can call at any time to move around or go to the toilet and that the barriers are an essential safety measure for the study; if the patient perfectly self-positions in the prone position, barriers would be removed after the investigator’s decision; this must be recorded and justified in the medical record).
- Note the date and time of the end of the prone position in the notebook (by the patient or by a staff member).

Each day of hospitalization, at least two PP sessions during the day, with the objective to spend as much time as possible in PP if tolerated and a minimum of 2.5 hr of cumulative time in PP during the day.

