### Patient follow-up

In both groups, the rate of patients usually sleeping in the prone position will be collected at the beginning of the study. These data will be considered in the data analysis.

After randomization, the intervention will be performed according to the procedure detailed above.

The criteria for prone position intolerance are as follows:

- feeling of respiratory discomfort or any other uncomfortable feeling for the patient.

If any of the above criteria appear, we will record them in the specific case report form.

The standard surveillance will be applied by staff members of the enrolling wards. The staff will be free to consider whether a patient should return to the supine position and/or increase the surveillance (e.g., more frequent monitoring of blood pressure, respiratory rate or SpO_2_). It will be recorded in the case report form (CRF).

In the interventional group, an evaluation of SpO_2_ will be performed at the first session (to evaluate the clinical improvement after the first session):

- SpO_2_ measurement before PP
- SpO_2_ measurement just before the return to supine position at the end of the first session.

| *Actions* | *Day 0*  *(****Inclusion visit)*** | *Positions* | *End of treatment*  *(hospital discharge or intensive care unit with mechanical ventilation)* |
| --- | --- | --- | --- |
| *Diagnosis of COVID-19* | *X* |  |  |
| *Written consent of the patient* | *X* |  |  |
| *Fax of inclusion to the research department* | *X* |  |  |
| *Medical history* | *X* |  |  |
| *Usual sleeping position* | *X* |  |  |
| *Positioning techniques (PP/semi-sitting)* |  | *X* |  |
| *Improvement of 2 points on the WHO ordinal scale* |  |  | *X* |
| *Adverse events* | *X* | *X* | *X* |

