## Research duration

Inclusion period: Epidemic COVID-19 period

Duration of intervention: the study intervention will stop when one of the events is reached: initiation of non-invasive or invasive ventilation, death, or patient still hospitalized at day 28 without event. Patients hospitalized for > 28 days will continue to be followed in the study (rate of use of resuscitation, rate of use of non-invasive or invasive ventilation, death).

The duration of participation for each patient corresponds to the hospitalization duration (all wards combined), subject to AEs that would require a longer follow-up.

Total duration of participation in the study for the patient: length of hospitalization

Total duration of the study: 24 months

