The durations (of oxygen therapy, non-invasive ventilation, hospitalization), will be compared between groups by Mann-Whitney U test adjusted for stratification variables [KAWAGUCHI; Statistics in Biopharmaceutical Research; 2011]. The difference in duration (of oxygen therapy, non-invasive ventilation, hospitalization) between groups will be expressed by its median and 95% CI obtained by bootstrapping (2000 unstratified samples).

We will conduct a per-protocol analysis including only patients of the intervention group who laid in a prone position for at least 2 hr each day, and patients of the usual care group who never laid in a prone position.

The above analyses will be repeated in prespecified subgroups formed according to the stratification variables #2 and #3 (SpO2 and BMI).

No interim analysis is planned.

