## Definition of the exclusion period

Patients included in the study will be allowed to participate in another study EXCEPT a study assessing prone position in the COVID-19 in medical wards (i.e., outside the ICU) during the 28-day follow-up. If the patient is transferred to an ICU, the study intervention will stop and the ICU practitioners will be free to care for the patient as they wish. During the SARS-CoV-2 epidemic, in the absence of extensive knowledge about the best management modalities, clinical research evaluating the full range of drug and non-drug strategies is an international priority.

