# Appendices

Appendix 1: Illustration of prone positioning (PP) in spontaneously breathing patient

Appendix 2: PP schedule collection

Appendix 3: Example of a follow-up worksheet in the control group

Appendix 4: WHO ordinal scale (according to CAO ; N Eng J Med ; 2020)

APPENDIX 1: Illustration of prone positioning (PP) in spontaneously breathing patient

1. **PUT THE BARRIERS**
2. **KEEP THE CATHETERS AND LINES FREE AROUND THE PATIENT**
3. **ASK THE PATIENT TO LIE ON PRONE POSITION**
4. **NOTE THE START OF PRONE POSITION**
5. **GIVE PATIENT THE CALLBELL for call the staff if necessary**
6. **EXPLAIN TO THE PATIENT THAT THEY MUST LIE 30 min to 1 HOUR PER SESSION (minimum)**

[figure not shown]

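### The per-protocol cut of 2 hr lies below the protocol's own 2.5 hr daytime minimum and is worded two ways, and the end of the intervention is contradictory for a patient moved to the ICU without ventilation

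*Protocol*

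**What the plan says.** **Daily dose.** The synopsis asks for at least two daytime sessions and "a minimum of 2.5 hr cumulative time in PP during the day". Section 4.4, on drawbacks, says "we propose a minimum of two PP sessions during the day with a minimum cumulative time of 2.5 hr". Section 5.2 says "a minimum of 2.5 hr of cumulative time in PP during the day", but earlier in the same section, and in 5.1, the 2.5 hr is called an objective. Appendix 1 gives the instruction "EXPLAIN TO THE PATIENT THAT THEY MUST LIE 30 min to 1 HOUR PER SESSION (minimum".

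**Per-protocol set.** Section 8.1 includes, from the prone arm, "only patients of the intervention group who laid in a prone position for at least 2 hr each day", and from the control arm those who never lay prone. Section 8.6 keeps the 2 hr figure but refers to daytime and drops the requirement that it be met daily.

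**End of intervention.** Section 5.4 lists "initiation of non-invasive or invasive ventilation, death, or patient still hospitalized at day 28 without event", and the synopsis gives the same list. Section 11.4 says "If the patient is transferred to an ICU, the study intervention will stop". The visit table in 5.3 heads its end-of-treatment column "hospital discharge or intensive care unit with mechanical ventilation".

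**The concern.** A per-protocol set should contain patients treated as the protocol specifies. Here the analysis sections admit patients whom the intervention sections describe as below the minimum, and no tolerance is stated or explained. Sections 8.1 and 8.6 can also select different patients. A requirement for every day, read literally, removes a patient for one short day, including the partial days of randomisation, transfer or discharge.

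The days that count depend on when the intervention ends, and the protocol gives different answers for an ICU transfer without ventilation. At stake are the consistency of what sites deliver and the membership and interpretation of the planned per-protocol analysis.

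**Working it through.** **1. Dose against cut-off.** Both figures are on the same scale, because night-time hours are not monitored (5.1) and the Appendix 2 log covers daytime only.

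- Stated minimum: 2.5 hr = 150 min.
- Per-protocol cut: 2 hr = 120 min.
- Gap: 150 − 120 = 30 min; 120/150 = 80%.

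Two 60-minute sessions every day satisfy 8.1 and miss the minimum in 5.2.

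**2. Appendix 1.** Two sessions at the stated floor give 2 × 30 = 60 min to 2 × 60 = 120 min, which is 30 to 90 min short of 150. Reaching 150 min takes 150/2 = 75 min per session with two sessions. At the floor it takes 150/30 = 5 sessions, or 150/60 = 2.5, so 3 sessions. The statements can therefore all be met together, but not by doing only the minimum on each.

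**3. End of intervention, patient moved to the ICU without ventilation.**

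| Source | Intervention stops? |
| --- | --- |
| Synopsis, 5.4 | No (needs ventilation, death or day 28) |
| Visit table, 5.3 | No (needs discharge, or ICU with mechanical ventilation) |
| 11.4 | Yes |

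The case is realistic. High-flow oxygen is allowed at entry (4.1), ICU transfer is a secondary endpoint in its own right, and the background section puts ICU access at 15% to 30% against mechanical ventilation at 10% to 25%.

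**4. How strict an every-day rule is.** The protocol gives no adherence figure. Assume 90% adherence on any day, independent between days, and 268/2 = 134 patients in the prone arm.

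- 5 days: 0.9^5 = 0.590, about 79 patients.
- 7 days: 0.9^7 = 0.478, about 64.
- 10 days: 0.9^10 = 0.349, about 47.

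**5. Direction of bias with no true effect.** Take a 17% failure rate, the midpoint of the 10% and 24% in section 8.2. Everything else here is assumed.

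- *Failures stop early.* With 0.9 per day, failures on day 3 and non-failures staying 5, 7 or 10 days, failures are retained with probability 0.9^3 = 0.729. The per-protocol failure rate is 0.17 × 0.729 / (0.17 × 0.729 + 0.83 × r). For r = 0.590, 0.478 and 0.349 this gives 20.2%, 23.8% and 30.0% against 17%, an apparent harm of about 3 to 13 points.
- *Sicker patients stop proning.* With half non-adherent at double the risk, adherers fail at 0.17/(0.5 + 0.5 × 2) = 11.3%, an apparent benefit of 5.7 points. At 1.5 times the risk, 0.17/(0.5 + 0.5 × 1.5) = 13.6%, or 3.4 points.

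Both mechanisms are plausible and they act in opposite directions. The control arm has its own, different filter. Read literally, never lying prone also removes controls who slept prone at night, which the synopsis and 5.2 allow.

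**6. Sample size.** With 4% vs 14%, two-sided 5%, 80% power and pooled variance, the need is 128 per arm, 256 in total, and 256/0.98 = 262 after 2% loss. The planned 268 covers this, and no adherence figure enters the calculation.

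**The case against.** The Appendix 1 times and the two-session rule are floors, not ceilings. Longer or additional sessions meet every statement, and the Appendix 2 log prints seven session rows. That stands, so Appendix 1 is a lesser inconsistency.

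The 2.5 hr is in places an objective, and a cut below a target can be a deliberate tolerance. That would be acceptable if stated, but the synopsis, 4.4 and 5.2 call it a minimum and no tolerance is given.

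Ending at discharge is implicit, since sessions are prescribed for each hospital day, and one source is only a column heading. That also stands. The conflict is confined to ICU transfer without ventilation, where 11.4 departs from the other three places.

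Handling of partial days could be left to an analysis plan. However, 8.1 already fixes a literal every-day rule, so the protocol states this rather than leaving it open.

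A reader might infer that the per-protocol result is biased in favour of prone positioning, by about 5.7 points, because controls are not filtered. The documents do not support this. Controls are filtered, though differently. The 5.7 points rest on an assumed non-adherence rate and risk ratio, and equally simple assumptions about early failures reverse the sign.

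**Conclusion.** The point holds as a set of conflicting statements that should be corrected. The per-protocol cut is 30 minutes (20%) below the stated daytime minimum. Sections 8.1 and 8.6 define the set differently. The intervention's end is contradictory for ICU transfer without ventilation. None of this rests on assumed figures.

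The retention and bias calculations do rest on assumptions. They show that an every-day rule may discard much of the prone arm and that the resulting bias could go either way; they do not establish its size or sign. The per-protocol comparison should be read as supportive only. The consequences are limited to delivery of the intervention and that secondary analysis. The intention-to-treat primary analysis and N = 268 are untouched.

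**What to change.** - Reconcile 5.1, 5.2, Appendix 1, 8.1 and 8.6, with the synopsis and 4.4, so that one daily dose statement and one per-protocol definition appear and agree. If the cut is meant to differ from the dose, state the tolerance and justify it.
- Reconcile 5.4, 11.4 and the visit table, with the synopsis, to a single rule for the end of the intervention. Which dose and which rule is for the trial team to decide; this review proposes neither.
- Count per-protocol adherence only over full ward days up to that end, and use the same wording in 8.1 and 8.6.
- State that the per-protocol result is supportive only, because adherence is observed after randomisation and the two arms are filtered differently.

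The cost is wording in a few sections, one table heading and one appendix page. Session dates and times are already logged under 5.6 and Appendix 2, so no new data collection or change in sample size is needed.

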A session of PP as long as possible at night. Patients will be encouraged to sleep in PP as much as possible at night, knowing that monitoring the number of hours will not be feasible in COVID-19 medical wards in the current context.

Bedridden patients who are not able to self-position to the prone position or with minimal assistance of one person will not be included in the study.

Barriers will be positioned to avoid the potential fall out of bed.

The patient will be allowed to choose the best PP as long as the back of the thorax is not compressed by the bed.

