### Semi-sitting in a bed or chair

The semi-sitting position in the bed is a minimum of 30° inclination, not more than 60% to 70% to avoid compression of the abdomen.

The patient can be installed in a chair if they wish. In this case, the position will be mentioned in the notebook.

The prone position is not authorized during the daytime. It is allowed at night only if it is the natural sleeping position.

Lateral position is authorized outside the intervention periods if the patient wishes and will be recorded.

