## Selection of participants to be included in the analysis

The main analysis will be conducted on an intention-to-treat basis. However, data for patients withdrawing their consent during the study, in accordance with French law, will not be analyzed.

A per-protocol analysis including only patients who performed at least 2 hr of PP during the day in the PP group and patients in the usual care group who did not perform PP, is planned.

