APPENDIX 3: Example of a follow-up worksheet in the control group

| **Day 1: Date =** | | | |
| --- | --- | --- | --- |
| Chair  Yes/No | Semi-sitting position  Yes/No | Walking around  Yes/No (toilette, transfer alone) | Lateral position: Yes/No |
| **Day 2: Date =** | | | |
| Chair  Yes/No | Semi-sitting position  Yes/No | Walking around  Yes/No (toilette, transfer alone) | Lateral position: Yes/No |
| **Day 3: Date =** | | | |
| Chair  Yes/No | Semi-sitting position  Yes/No | Walking around  Yes/No (toilette, transfer alone) | Lateral position: Yes/No |
| **Day 4: Date =** | | | |
| Chair  Yes/No | Semi-sitting position  Yes/No | Walking around  Yes/No (toilette, transfer alone) | Lateral position: Yes/No |
| **Day 5: Date =** | | | |
| Chair  Yes/No | Semi-sitting position  Yes/No | Walking around  Yes/No (toilette, transfer alone) | Lateral position: Yes/No |
| **Day6: Date =** | | | |
| Chair  Yes/No | Semi-sitting position  Yes/No | Walking around  Yes/No (toilette, transfer alone) | Lateral position: Yes/No |

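### The per-protocol rule for usual care requires patients who never lay prone, although the protocol lets them sleep prone at night, so it excludes adherent controls in one arm only

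*Protocol*

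**What the plan says.** **Per-protocol set.** Section 8.1 keeps, on the usual-care side, only "patients of the usual care group who never laid in a prone position". Section 8.6 restates the set as "patients in the usual care group who did not perform PP". The daytime qualifier in that sentence belongs to the other arm: "at least 2 hr of PP during the day in the PP group".

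**What controls may do.** Section 5.2, on the semi-sitting position, states: "The prone position is not authorized during the daytime. It is allowed at night only if it is the natural sleeping position". The synopsis gives the same rule under study design.

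**What is recorded.** The example control worksheet in Appendix 3 has four daily items: chair, semi-sitting, walking around, and "Lateral position: Yes/No". None is prone. The CRF list in section 5.6 has number and duration of prone sessions, with no arm named for those rows. The session diary in Appendix 2 covers daytime. For nights, section 5.2 encourages prone sleep in the intervention arm, "knowing that monitoring the number of hours will not be feasible in COVID-19 medical wards in the current context", and section 5.1 also says that night-time duration will not be monitored. Usual sleeping position is collected once, at inclusion, in both groups (section 5.3), and is to be considered in the analysis.

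**The concern.** A per-protocol set should keep patients who followed the protocol. Here a usual-care patient who sleeps on the stomach by habit, as section 5.2 permits, has lain prone and so fails the wording of section 8.1. That patient is adherent but excluded.

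The exclusion works in one arm. A habitual prone sleeper randomised to the intervention is not removed for that habit, because the rule there concerns hours of daytime prone. The two per-protocol arms would then differ in a baseline characteristic because of the selection rule itself. If the habit is related to outcome, for example through body build, the comparison is biased in a direction that the protocol gives no means of predicting.

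There is also a recording gap. The rule in section 8.1 covers the whole day and night, yet no route is stated for recording night-time prone in controls, and the example worksheet does not prompt for prone at any hour. Different centres or analysts could assign the same patient differently.

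**Working it through.** **1. Consistency check.** Three types of control patient, taken through the rules:

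| Control patient | Section 5.2 and synopsis | Section 8.1 as written | Section 8.6 as written |
|---|---|---|---|
| Never prone | adherent | kept | kept |
| Prone at night only, natural position | adherent | excluded | unclear: depends on whether sleeping prone counts as performing PP |
| Prone by day | not adherent | excluded | excluded |

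The second row is the contradiction. A rule based on daytime prone would agree with section 5.2 in all three rows.

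**2. The plan's own sample size.** Inputs from section 8.2 and the synopsis: two-sided alpha 0.05, power at least 80%, 4% vs 14% or 10% vs 24%, loss below 2%, allocation 1:1, N = 268. The pooled-variance normal approximation gives

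power = Φ[(d − 1.96·SE0)/SE1], with SE0 = √[p̄(1 − p̄)(1/n1 + 1/n2)] and SE1 = √[p1(1 − p1)/n1 + p2(1 − p2)/n2],

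where d is the difference in rates and p̄ is the rate pooled over both arms.

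- 4% vs 14% at 80% power needs 128 per arm, 256 in all, or 262 after dividing by 0.98. This is within 3% of 268.
- At 134 per arm, power is 82.0% (4% vs 14%) and 86.7% (10% vs 24%).
- With 2% loss, 134 × 0.98 ≈ 131 per arm, and power is 81.1% and 85.9%.

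The stated 80% is reproduced. It refers to the main analysis and does not depend on the per-protocol definition.

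**3. Size of the exclusion in the per-protocol set.** The protocol does not say what share of controls sleep prone. Assume 10% or 20%, keep 131 in the prone arm, and leave the event rates unchanged:

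| Controls dropped (assumed) | Prone arm / controls | Power, 4% vs 14% | Power, 10% vs 24% |
|---|---|---|---|
| 0% | 131 / 131 | 81.1% | 85.9% |
| 10% | 131 / 118 | 79.4% | 84.2% |
| 20% | 131 / 105 | 77.4% | 82.1% |

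Worked example, 10% vs 24% with 118 controls: p̄ = (131 × 0.10 + 118 × 0.24)/249 = 0.1663; SE0 = 0.0473; SE1 = 0.0473; (0.14 − 1.96 × 0.0473)/0.0473 ≈ 1.00; Φ ≈ 0.84.

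The loss of precision is therefore small. The selection bias cannot be sized from the document, because neither the frequency of the habit nor its relation to outcome is given.

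**The case against.** The strongest reply has four parts.

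*The per-protocol analysis is only supportive.* This stands. The main analysis is by intention to treat, so the primary test and the sample size are untouched.

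*Section 8.6 can be read more narrowly.* Performing PP may mean the study procedure, that is, daytime sessions, in which case night sleepers stay in. The reading is possible, but section 8.6 attaches the daytime limit to the intervention arm only, and section 8.1 says never. The two sections still need reconciling.

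*Control prone positioning can be recorded.* This stands in part. The prone-session rows in section 5.6 name no arm, whereas the SpO2 row in the same table is expressly limited to the intervention group. Appendix 3 is labelled an example, and section 12.1 requires an explanation for each missing item. A reader might infer that the rule cannot be applied at all, that prone exposure in controls is wholly unmeasured, or that a blank will be taken as never prone. The document does not support these readings. The gap is limited to night-time prone and to the missing prompt on the example control sheet.

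*Not counting night hours is a stated pragmatic choice.* This stands, and the correction does not require counting them.

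**Conclusion.** The point holds as an inconsistency in the definition of a supportive analysis. Sections 8.1 and 8.6 do not agree with the synopsis and section 5.2, and the literal rule excludes adherent controls in one arm only. Under an assumed exclusion of 10% to 20% of controls, with no losses from the prone arm beyond the 2% and unchanged event rates, per-protocol power falls by about 2 to 4 percentage points in either design scenario. The more important effect is a possible selection bias of unknown size and direction.

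A reader might go further and treat this as a loss of power in the trial through controls crossing over to prone, or conclude that a null result could not be explained. Neither follows. Crossover would dilute the intention-to-treat contrast whatever the per-protocol wording says, and a clearer definition would not restore that power. Baseline sleeping position is available in both groups to identify habitual prone sleepers.

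**What to change.** 1. In sections 8.1 and 8.6, define the usual-care per-protocol set in the same words, as patients with no daytime prone positioning, and state that night-time prone permitted under section 5.2 does not exclude a patient.
2. Add one daily item to the control worksheet, *prone during daytime: yes/no*, to feed the prone fields already listed in section 5.6.
3. Add a sensitivity analysis of the per-protocol comparison by usual sleeping position at inclusion, applied in the same way to both arms.

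The cost is one sentence in each of two sections and one tick box per control patient-day. No hours need to be counted at night, and neither patient care nor the sample size changes. The worksheet item should be in place before recruitment, or as early as possible, because exposure not noted on the ward is hard to recover later.
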